**External Training**		

Cornell Empowering Families Project	New York State program for CHWs. Topics include: relationship and communication skills; cultural competence; working with low-literacy patients; needs assessment; empowerment; CHW self-care	The Cornell Project
Simulated Patient Training	Simulated patients, with video-taping and feedback	Local, private agency that provides standardized patients for medical training
NCI/ACS^a ^Navigator Training Summit	4 day program with navigators from across the US	

^a^HIPAA = Health Insurance Portability and Accountability Act; NCI = National Cancer Institute; ACS = American Cancer Society

All of the navigators completed the training program prior to working with patients. The success of navigator training was evaluated in several ways. The core CHW curriculum (The Cornell Project) required post-testing to obtain certification. In addition, PN's were regularly observed by their supervisor during patient encounters. Encounter forms were checked for accuracy and consistency. Computer skills were supervised to ensure minimal standards were met. Passing scores on tests for research ethics certification and patient confidentiality were required. PN's were also pre- and post-tested at national training sessions.

### Characteristics of Navigators

The first three PN's recruited were females: one African-American and two Puerto Rican-Americans who were fluent in Spanish. Over time, three additional Navigators have been hired and trained, including two African-American females and one white male. None of the PN's had any previous medical training; however, PN's had previous experience with health insurance enrollment, being a patient in the medical system, and/or previous community work experience.

### Supervision for Navigators

Navigators are supervised by a master's level social worker with experience in clinical supervision, teaching, research, and work in primary care. The navigator supervisor provides real-time consultation and supervision of case management, through weekly meetings with each of the navigators, cell phone contact, review of documentation, and review of selected audiotapes (with patients' consent) of meetings between navigators and patients. Supervision also includes professional support of the PN's, recognizing the emotionally intense work they are doing and promoting self-care to minimize "burnout". Quarterly, each PN is directly observed by the supervisor in patient interactions to ensure that basic competencies continue to be met.

### Description of the Navigation Intervention

After enrollment and completion of baseline data collection, patients are randomly assigned to standard care or patient navigation-activation. Patients assigned to navigation are contacted within three days by their PN to assess their needs. PN's conduct a semi-structured assessment interview in-person or over the phone to identify barriers to care. Table 3 lists the types of barriers that PN's were trained to address. Navigators also immediately become involved in performing proactive services on the patient's behalf, such as appointment reminders, in order to prevent delays in receiving treatment or follow-up care with their medical provider.

**Table 3 T3:** The Navigation-Activation Intervention

Phase 1: Patient Intake	Identify Barriers to Quality Care
	Transportation
	Housing
	Insurance
	Literacy
	Language
	Child Care/elder care
	Family/Community Supports
	Geographic Distance from Health Care
	Adequate Health Insurance
	Financial Problems
	Work Schedule
	Medical Communication Concerns
	Fear
	Comorbid Illnesses
	Disability
	Perceptions/Beliefs about Treatment
	Systems Problems with Scheduling Care
	Attitudes toward Providers
	Other
**Phase 2: Patient Navigation-Activation**	**Address Barriers**
	Provide Information
	Provide Pre-Appointment Coaching
	Provide Emotional and Social Support
	Provide Appointment Reminders
	Link to Resources

**Phase 3: Assessment of Intervention**	**Outcomes**
	Time to Completion of Treatment
	Treatment Guideline-Compliant Care
	Patient Satisfaction
	Patient Knowledge and Self-Efficacy

After identifying the patients' barriers to care, the PN uses a variety of strategies to address the barriers. Actions taken by the PN include: supportive contact with the patient, such as face-to-face meetings, telephone, email or regular mail correspondence; identifying and linking patients to social or financial resources and appropriate community supports; helping with paperwork, obtaining records, scheduling appointments, following-up on test scheduling or results; and accompanying the patient to appointments to help coach as well as providing emotional support.

Navigators provide patients with approved educational materials and promote treatment adherence. Navigators facilitate coordination of care by ensuring that consultation reports, test results, and new prescriptions or prescribed treatments are available to all providers at the time of an appointment. Navigators notify providers when a patient misses an appointment or treatment or experiences new or changed symptoms. Navigators are specifically trained to effectively interact with professional health care personnel.

For patient activation, PN's offer all patients coaching in communication skills. Navigators meet with patients prior to appointments and assist patients in identifying one to three concerns they wish to address during their visit, and create question lists as tools for patients to use during visits. Patients rehearse how to ask questions, follow-up when they are unclear about the response they receive, and re-state the plan to confirm understanding. Though often present during visits, PN's encourage patients to assume an active role during visits, rather than speaking for them. Navigators debrief with patients following the medical visits, to identify and clarify potential areas of confusion.

### Tailored Intensity of Navigation

Participating patients receive navigation of differing intensity depending on their access barriers, needs, and resources. Patients who report few or no access barriers and report no need for navigation services receive *low-intensity navigation*. For example, a woman with an abnormal mammogram who requires no assistance and does not desire coaching in communication receives support and reminder phone calls only. *High intensity navigation *is indicated for a patient with cancer who faces access barriers to care or who experiences significant complications from treatment requiring intensive coordination of care among providers.

In summary, the navigation-activation intervention is designed to identify barriers, assist patients in overcoming them, provide emotional support, improve patient understanding of his or her condition and treatment, empower the patient to become actively involved in his or her care, improve adherence to treatment, and promote patient satisfaction with health care. Thus, the intensity of navigation is tailored to the needs of the patient.

### Patient Accrual and Study Flow

The clinical trial began in 2005 with a planning and development phase followed by recruitment of three CHW navigators and a supervisor in 2006. Three hundred forty-four patients have been recruited into the program, and 178 were randomly assigned to the navigation-activation intervention group, following informed consent. In addition to the planned assessments, semi-structured exit interviews are also being conducted with all subjects as they complete the program to assess their cancer-treatment experiences and their experiences with the navigators, for quality control.

While the study is still on-going, we can report that common barriers identified and addressed by the patient navigators include financial difficulties, lack of health insurance, lack of social support, lack of transportation, difficulty communicating with health care providers, and limited English proficiency. In addition to planned help provided by our navigators to address these barriers, navigators also help patients organize and follow-through with doctors' appointments, and helping them understand medical information.

### Planned Analytic Approach

The primary outcome measures for this clinical trial include time to completion of treatment (or to diagnostic resolution in the case of patients with positive screening tests), patient satisfaction, and cost. Details regarding each of these measures are as follows:

#### Time to completion of cancer treatment

This measure is defined based on review of medical records following completion of treatment for oncology subjects. It will be assessed based on time (in days) from the date of the initial oncology/surgical consultation to completion of cancer treatment (e.g. surgery, chemotherapy regimen, or radiation, whichever occurs last).

#### Health care satisfaction

We hypothesize improvements in satisfaction with health care. Baseline satisfaction is measured using a newly created patient satisfaction with cancer care (continuous measure). It is assessed at baseline for all subjects and at three months for primary care subjects and at three months, six, nine and twelve months for subjects with cancer or at the end of treatment.

#### Costs of navigation

We assess the costs of navigation including supervision. We assess the costs of navigator time by asking navigators to track their time spent on navigaton-related functions. These include training time and in-services, meetings with supervision, entry of data for subjects assigned to navigation, phone calls related to navigation, meetings with subjects and families, meetings and phone calls with providers and office staff, and travel time. The proportion of time devoted to navigation will be multiplied by navigator cost (salary plus benefits). Additional expenses include costs for supervision, transportation, child care, and patient educational materials. Patient navigator supervision time will be based on the percent of time related to navigation. We also collect data (e.g. medical records) needed to estimate the health care costs of subjects assigned to either navigation or usual care. Subjects are also asked to estimate time (nearest day) that they missed work to visits or disability.

Secondary outcome measures for this study are guideline concordant care, patient adherence, health literacy, patient activation, medical knowledge, and functional health status. Details regarding analysis of these outcomes include:

#### Patient adherence to recommendations

We will measure patient adherence from both chart abstraction and patient report. Patient adherence to diagnostic recommendations is based on the percentage of missed appointments for diagnostic testing. Subject adherence to treatment is assessed based on the percent of recommended courses of radiation received or percentage of full chemotherapy received and percentage of cancer visits that are missed. We also are measuring relative dose intensity (RDI) for breast cancer patients who receive chemotherapy. RDI is a standard measure of optimal chemotherapy dosing. Dose intensity is amount of drug delivered per unit time typically standardized to body surface area as mg/m^2^/week. The RDI is the ratio of the dose intensity actually received relative to optimal dose intensity.

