### Patient Navigation

For more than 40 years, community health workers (CHW's) have enhanced access to care among underserved populations in the United States (US)[16,17]. Freeman *et al *reported that 87% of inner-city patients with abnormal cancer findings who received PN from CHW's completed recommended biopsies compared to only 57% among those who were not navigated[18]. More recently, CHW's have been shown to improve outcomes in prenatal care[19], smoking cessation[20], child[21] and adult immunizations[22], and diabetes and depression management[23].

Patient navigation programs for cancer-related care have been developed across the US, including more than 100 PN programs sponsored by the American Cancer Society. Most PN programs share a number of common characteristics. Navigators assist patients with abnormal cancer screening or diagnostic tests by identifying and addressing barriers to quality and timely health care. For example, PN's may help patients keep track of appointments, interpret medical information, and provide social support[24].

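### Diagnostic adherence is scored on missed appointments, so a recommended test that is never scheduled is not counted, and navigators schedule appointments in one arm only

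*Protocol article*

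**What the plan says.** Patient adherence is listed among the secondary outcomes of the protocol article. The section Patient adherence to recommendations names the sources: "We will measure patient adherence from both chart abstraction and patient report". For diagnosis the definition is: "Patient adherence to diagnostic recommendations is based on the percentage of missed appointments for diagnostic testing". For treatment, the next sentence uses the "percent of recommended courses of radiation received or percentage of full chemotherapy received", together with the "percentage of cancer visits that are missed".

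The section Description of the Navigation Intervention lists, among navigator actions, "helping with paperwork, obtaining records, scheduling appointments, following-up on test scheduling or results". It also describes proactive services "such as appointment reminders, in order to prevent delays in receiving treatment or follow-up care". Control patients receive usual care.

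In the background section Patient Navigation, the article supports navigation with a cited study in which 87% of navigated inner-city patients with abnormal findings "completed recommended biopsies compared to only 57% among those who were not navigated".

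**The concern.** The outcome is called adherence to recommendations, but its diagnostic component does not refer to what was recommended. A patient told to have a biopsy who never arranges it has no missed appointment. The score is 0/0, or 0% missed if that is how it is filled in. A patient whose navigator arranges the biopsy, and who misses that one appointment, scores 100% missed. Neither patient had the test.

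Getting tests scheduled is part of what navigation does, so the intervention acts on the denominator of the measure meant to evaluate it. That part of any benefit is invisible, and the additional patients brought into the schedule become the ones who can be counted as missing. The radiation component in the same paragraph avoids this, because care that never starts counts against it.

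**Working it through.** **The plan's own figure.** The article gives no expected rate for diagnostic adherence. Sample Size Determination states detectable differences of 16 points (200 patients) and 13 points (300 patients) from a 75% control rate, and extends them to adherence rates. Taking 1:1 allocation and a two-sided 5% level (an assumption, as none is stated), the continuity-corrected requirement is 98 per arm (196) for 75% against 91%, and 154 per arm (308) for 75% against 88%. Both are within 3% of the stated totals. Without the correction, power is 86% and 83%. These figures reproduce, and the point does not depend on them.

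**General form.** Let b be the share of recommended tests that are scheduled and m the share of scheduled tests that are missed.

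- Measure as written: missed / scheduled = m
- Recommended tests not done: 1 − b(1 − m)

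The measure does not contain b. The article gives neither b nor m, so all values here are assumed:

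| b control, navigated | m control, navigated | Measure as written | Recommended tests not done |
|---|---|---|---|
| 0.70, 0.95 | 10%, 10% | no difference | 37.0% vs 14.5%: 22.5 points better |
| 0.70, 0.95 | 10%, 15% | 5 points worse | 37.0% vs 19.25%: 17.75 points better |
| 0.70, 0.95 | 10%, 5% (reminders work) | 5 points better | 37.0% vs 9.75%: 27.25 points better |
| 0.90, 0.95 | 10%, 12% | 2 points worse | 19.0% vs 16.4%: 2.6 points better |
| 0.70, 0.70 | 10%, 5% | 5 points better | 37.0% vs 33.5%: 3.5 points better |

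In the last row scheduling is equal, and the measure slightly overstates the gain (1 − 0.70 × 0.95 = 33.5%).

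**Illustration on the article's cited rates.** Take one recommended test per patient and completion of 87% navigated and 57% not navigated. The true difference in non-completion is 43 − 13 = 30 points. Assume that every navigated patient is booked and that a share u of control non-completers never book.

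- Control, missed / booked = 43(1 − u) / (100 − 43u)
- Navigated, missed / booked = 13 / 100 = 13%

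| u | Control | Navigated | Apparent benefit |
|---|---|---|---|
| 0 | 43/100 = 43.0% | 13.0% | 30.0 points |
| 0.5 | 21.5/78.5 = 27.4% | 13.0% | 14.4 points |
| 0.8 | 8.6/65.6 = 13.1% | 13.0% | 0.1 points |
| 0.9 | 4.3/61.3 = 7.0% | 13.0% | 6.0 points worse |

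If never-booked patients are scored 0% missed instead, the benefit is gone when 43(1 − u) = 13, that is u = 30/43 = 0.70.

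**Relaxing the booking assumption.** If half of navigated non-completers also never book, the navigated figure is 6.5/93.5 = 7.0%. At u = 0.5 the apparent benefit is then 27.4 − 7.0 = 20.4 points. At u = 0.8 it is 13.1% against 7.0%, and it disappears only at u of about 0.90.

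**The case against.** Several parts of the case on the other side stand.

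- **Direction.** A reader might infer that the error always runs against navigation. The documents do not support that. Reminders act directly on missed appointments, and the table above has rows in which the measure favours navigation.
- **Reversal.** A reader might infer that a benefit would vanish or reverse. On the cited rates that needs u of about 0.7 to 0.9, in most cases with every navigated patient booked. The rates come from another study's inner-city patients with abnormal findings.
- **Charting.** The article says "Navigators notify providers when a patient misses an appointment or treatment", from which a reader might infer that misses are recorded more fully in the navigated arm. Nothing says that practices fail to record their own missed visits in either arm, so this is conjecture.
- **Other outcomes.** The trial is not blind to unscheduled tests. They would lengthen time to diagnostic resolution, a primary outcome for positive-screen patients (Planned Analytic Approach). They could also count against guideline concordance, which covers diagnostic management, and may show in the self-report adherence items of Table 1. None of these repairs the ratio, which would still be reported as adherence.
- **Cancer visits.** The missed-visit percentage has a similar form, but the radiation and chemotherapy components beside it catch treatment that never starts. It is not an equal flaw.
- **Population.** The Discussion says that navigation for screening was no longer needed and that recruitment moved to cancer centers, so diagnostic testing may concern few patients.
- **Condensation.** The article's wording is a summary, and a fuller protocol may handle unscheduled tests. However, the text gives a definition with a stated numerator, and taken as written it leaves unscheduled tests out.

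**Conclusion.** The point holds as a weakness in one component of a secondary outcome. That the stated measure ignores unscheduled tests, and that navigators schedule in one arm only, follows from the text. The size does not, because the article gives no scheduling or miss rates. With the cited completion rates, all navigated patients booked and half of control non-completers never booking, a true 30 points shows as 14.4, less than half. Under milder assumptions the loss is smaller, and with equal scheduling in both arms there is no reversal.

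The supported conclusion is that the measure can understate, and in more extreme cases hide or reverse, a real gain when navigation raises scheduling. The documents do not show that it will do so, or that the trial's main conclusions are affected.

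**What to change.** In both arms, define diagnostic adherence as the percentage of chart-documented recommended diagnostic tests that were completed within a window fixed in advance, and count a test never scheduled as not completed. This matches the recommended-courses basis already used for radiation. Keep the missed-appointment percentages, for diagnostic testing and for cancer visits, as descriptive results.

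The charts are already abstracted for adherence, so the cost is about one extra field recording what was recommended and a revised definition. There are three downsides. With 344 patients already recruited, this changes a secondary outcome during the trial, so it must be dated and documented before outcomes are analysed by arm. It depends on recommendations being written in the chart, and that documentation could itself differ by arm. For positive-screen patients it partly overlaps with time to diagnostic resolution, which should be acknowledged when both are reported.

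### RDI is compared between arms only in breast cancer patients who receive chemotherapy, a group formed after randomisation that navigation may change

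*Protocol article*

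**What the plan says.** The article names adherence as a secondary outcome (list at the end of the section Costs of navigation): "Secondary outcome measures for this study are guideline concordant care, patient adherence, health literacy, patient activation, medical knowledge, and functional health status".

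The section Patient adherence to recommendations measures treatment adherence by "percent of recommended courses of radiation received or percentage of full chemotherapy received and percentage of cancer visits that are missed". It then adds RDI for a restricted group: "We also are measuring relative dose intensity (RDI) for breast cancer patients who receive chemotherapy". The definition follows: "The RDI is the ratio of the dose intensity actually received relative to optimal dose intensity".

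The section Description of the Navigation Intervention gives the timing: "After enrollment and completion of baseline data collection, patients are randomly assigned to standard care or patient navigation-activation". Its Table 3 lists fear and "Perceptions/Beliefs about Treatment" among the barriers navigators are trained to address, and the text adds: "Navigators provide patients with approved educational materials and promote treatment adherence". Eligibility rests on a new diagnosis or a positive screening test, not on being on chemotherapy.

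Data Analysis compares continuous measures between the randomised groups by two-sample t-test. The article does not say how a patient who is recommended chemotherapy and never starts is handled in any adherence measure.

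**The concern.** RDI is listed as a measure of adherence, but a patient enters the comparison only by receiving chemotherapy. Someone who was recommended it and never began has no RDI and drops out, although that is complete non-adherence to the recommendation.

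Because the intervention is meant to act on barriers to treatment, the two groups of recipients may differ in make-up even though the arms were balanced at randomisation. The t-test would then mix two things: any effect of navigation on dosing in patients who would have started anyway, and the presence of extra starters in the navigated arm. If those extra starters have more delays or reductions, the navigated arm's mean RDI falls while more recommended chemotherapy is delivered overall. A reader of the RDI result alone could draw the wrong conclusion about adherence.

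**Working it through.** **Figures in the article.** None is given for RDI or for the proportion starting chemotherapy. The sample-size figures concern treatment completion at nine months and a general standardised difference in means. They supply no input here, and the point does not depend on them. All numerical inputs below are therefore assumptions.

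**Set-up.** Among patients recommended chemotherapy, let
- a = share who start in either arm
- b = share who start only if navigated
- m_a = mean RDI of those who start in either arm
- m_b = mean RDI of those started by navigation
- g = gain in RDI from navigation in those who would start anyway

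Control recipients have mean m_a. Navigated recipients have mean [a(m_a + g) + b·m_b]/(a + b).

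Difference, navigated minus control:
- recipients only: [a·g + b(m_b - m_a)]/(a + b)
- all recommended, never-starters at 0: a·g + b·m_b

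With g = 0, the first is negative whenever m_b < m_a, and the second is positive whenever b > 0 and m_b > 0.

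**Worked case.** a = 0.80, b = 0.10, m_a = 0.90, m_b = 0.60, g = 0.
- Recipients: (0.80 × 0.90 + 0.10 × 0.60)/0.90 = 0.78/0.90 = 0.867 versus 0.900, difference -0.033.
- All recommended: 0.72 + 0.06 = 0.78 versus 0.72, difference +0.06.

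**Varying the RDI of the added starters** (a = 0.80, b = 0.10, m_a = 0.90, g = 0):

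| m_b | Recipients only | All recommended |
|---|---|---|
| 0.50 | -0.044 | +0.05 |
| 0.60 | -0.033 | +0.06 |
| 0.70 | -0.022 | +0.07 |
| 0.75 | -0.017 | +0.075 |
| 0.85 | -0.006 | +0.085 |
| 0.90 | 0 | +0.09 |

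**Wider range.** With a from 0.70 to 0.90, b from 0.05 to 0.15 (a + b at most 1), m_a = 0.90, m_b from 0.60 to 0.85 and g = 0, the recipients-only difference runs from -0.053 to -0.003. The all-recommended difference runs from +0.03 to +0.13.

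**Where the sign is not fixed.** With g = 0.02 over the same range, the recipients-only difference runs from -0.036 to +0.016. It stays negative only when b(m_a - m_b) exceeds a·g. In the worked case, 0.10 × 0.30 = 0.030 exceeds 0.80 × 0.02 = 0.016, giving (0.016 - 0.030)/0.90 = -0.016. With m_b = 0.85, 0.10 × 0.05 = 0.005 does not exceed 0.016, giving (0.016 - 0.005)/0.90 = +0.012.

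**The case against.** The strongest reply is that RDI is by nature a measure in treated patients. It describes how close delivered dosing comes to the optimal level once treatment is given, so restricting it to recipients is ordinary practice. This stands as a description of the metric. It does not make the recipients-only contrast a randomised comparison of adherence.

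A second reply is that RDI is supplementary. The same section lists a chemotherapy percentage that the text does not restrict to recipients, and guideline-concordant care, judged by a blinded oncologist, covers therapeutic management. Either may register a patient who never starts. This also largely stands and limits the point. A reader might infer that all chemotherapy adherence is measured only in recipients; the article does not say that. Equally, it does not say that a never-starter scores 0% on the chemotherapy percentage, and a single yes/no concordance judgement does not correct a misleading RDI contrast.

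A reader might also infer two further faults from "percent of recommended courses of radiation received or percentage of full chemotherapy received": that the radiation measure counts never-starters as 0% and so conflicts with RDI, or that a patient recommended both modalities is scored on whichever was received. The documents support neither. Handling of radiation never-starters is not stated. The natural sense of the condensed sentence is that each modality has its own measure, and detailed scoring is commonly left to the full protocol or analysis plan.

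Finally, the size is wholly assumed. That is correct: the documents establish neither that navigation raises starts nor that added starters have lower RDI.

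**Conclusion.** The point holds for RDI. The article itself fixes the RDI population by an event that follows randomisation and that the intervention may change, so this is a stated choice and not a detail left to an unseen analysis plan. The comparison is open to selection bias if navigation changes who starts.

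It would be tempting to conclude that the adherence result will have the wrong sign. The documents do not support that. A reversal needs navigation to raise chemotherapy starts, added starters to have lower RDI, and any gain in other starters to be too small to offset them. The -0.033 against +0.06 shows that a reversal is possible and does not estimate the bias; other assumed inputs give zero or a positive recipients-only difference.

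The reach is modest: one added component of a secondary outcome, in breast cancer patients only. No primary outcome depends on RDI. The change is still worth making, because it is cheap and the article describes the study as ongoing, with formal evaluation at its end.

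**What to change.** 1. Base the between-arm comparison of chemotherapy adherence on all patients for whom chemotherapy was recommended, whether or not they start.
2. In that group, report initiation by arm, and the chemotherapy percentage with never-starters explicitly counted as 0%.
3. Label RDI among recipients as descriptive. Use RDI = 0 for never-starters at most as a sensitivity analysis.
4. Use recommended chemotherapy as the denominator, not guideline indication. The two populations differ: a patient whose clinician did not recommend chemotherapy, for example because of comorbidity, should not count as non-adherent to a recommendation. A recommendation may itself follow randomisation, so show the number recommended by arm as well. This reduces the selection problem but may not remove it.

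The cost is revised outcome wording, plus a little more abstraction and analysis. The article does not say that the chemotherapy recommendation is recorded separately from the overall concordance judgement, so it may have to be extracted. Counting never-starters as 0% puts a spike at zero, so a rank-based or two-part summary is needed beside the mean.
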